# The efficacy and safety of ginger supplementation in patients with multiple sclerosis: A rationale and study protocol for a double‐blind randomized controlled trial

**DOI:** 10.1002/hsr2.1004

**Published:** 2022-12-21

**Keywords:** ginger, interleukin‐17, matrix metalloproteinase‐9, multiple sclerosis, neurofilament protein L, nitric oxide

## Abstract

**Background and Aims:**

Multiple sclerosis (MS) is a chronic disease characterized by axonal damage, demyelination, inflammation, oxidative stress, and immune cell infiltration. This disease is the first cause of nontraumatic disability in young adults leading to a decline in patients' quality of life. Patients with MS may also suffer from gastrointestinal symptoms due to the disease or prescription drugs. Unfortunately, no treatment for MS has been discovered yet, and prescribed drugs can only help control its clinical course. Interestingly, recent animal studies have shown positive effects of ginger administration in the MS model. Therefore, we aim to determine the effect of ginger supplementation on neurofilament light chain, matrix metalloproteinase‐9, interleukin‐17, nitric oxide, complete and differential blood counts, disability status, quality of life, gastrointestinal symptoms, and body mass index (BMI) in MS patients.

**Methods:**

This study is a double‐blind randomized controlled trial. Fifty‐two patients with relapsing‐remitting MS will be assigned to intervention and control groups using stratified permuted block randomization. The intervention and control groups will take 1500 mg/day ginger and placebo (as corn) supplements for 12 weeks, respectively. All outcomes will be assessed before and after the trial. Serum concentrations of neurofilament light chain, matrix metalloproteinase‐9, and interleukin‐17 will be measured by enzyme‐linked immunosorbent assay. Nitric oxide serum levels will be detected using colorimetry. Complete and differential blood counts will be assessed by an automated hematology analyzer. Disability status, quality of life, and gastrointestinal symptoms will be evaluated by the Expanded Disability Status Scale, MS Impact Scale, and Visual Analog Scale, respectively. BMI will be calculated by dividing weight in kilograms by height in meters squared. Potential side effects of ginger supplementation will also be closely monitored during the study.

**Trial Registration:**

This protocol was registered at the Iranian Registry of Clinical Trials (www.irct.ir) under the registration number IRCT20180818040827N3.

## BACKGROUND

1

Multiple sclerosis (MS) is a chronic autoimmune, inflammatory, and degenerative disease of the central nervous system (CNS). The etiology of MS is unknown, but some environmental and genetic factors are likely to be contributed to its development. As an example, high body mass index (BMI) can increase the risk of developing MS by about twofold.^1^ Regarding clinical course, this disease is divided into four different subtypes including clinically isolated syndrome, relapsing‐remitting MS, primary progressive MS, and secondary progressive MS. The majority of patients with MS suffer from the relapsing‐remitting type, which is characterized by relapses of MS and periods of stability or remission between relapses.^2^ MS can lead to inflammation, oxidative stress, immune cell infiltration, demyelination, and axonal damage in the human body. Evidence has shown that neurofilament light chain, matrix metalloproteinase‐9, interleukin‐17, nitric oxide, and leukocyte differential count are reliable indicators of axonal damage, demyelination, inflammation, oxidative stress, and infiltration of immune cells in MS patients, respectively.^3^, ^4^ In addition, interleukin‐17 and nitric oxide have been shown to be involved in the pathology and immunomodulation of MS.^5^, ^6^ Unfortunately, no treatment for MS has been discovered so far, and prescription drugs can only help control its clinical course. Therefore, this disease is considered to be the first cause of non‐traumatic disability in young adults leading to a severe reduction in patients' mental and physical quality of life.^7^, ^8^ In clinical practice, the disability status of patients with MS is quantified by the Expanded Disability Status Scale (EDSS).^9^ The guidelines of the European Medicines Agency also suggest EDSS as a primary endpoint in MS trials.^10^ Moreover, gastrointestinal complications are often added to the problems of MS patients. Two‐thirds of them suffer from chronic gastrointestinal symptoms due to the disease or prescribed drugs. The most common symptoms reported by these patients include dysphagia, heartburn, nausea, dyspepsia, diarrhea, constipation, and fecal incontinence.^11^

Ginger (*Zingiber officinale* Roscoe) belongs to the family Zingiberaceae. It has been used as a food, spice, and flavoring for centuries in various societies, especially in Asian countries. It is a therapeutic plant and mainly used to improve gastrointestinal symptoms and relieve pain caused by inflammation in both traditional and modern medicine.^12^, ^13^ Although ginger has been reported to have poor bioavailability due to its low aqueous solubility and excessive phase II hepatic metabolism,^14^ many animal and human studies have shown positive effects after ginger supplementation.^15^ Based on the results of clinical trials, ginger consumption is beneficial for patients with diabetes,^16^ obesity,^17^ and migraine.^18^ It can also improve quality of life and reduce nausea, vomiting, and fatigue induced by chemotherapy in cancer patients.^19^ Moreover, previous studies have shown that ginger can reduce tumor necrosis factor‐alpha and interleukin‐1 beta in patients with knee osteoarthritis.^20^ Furthermore, ginger supplementation can regulate the expression of some inflammatory and immune‐mediating genes such as T‐box transcription factor 21, forkhead box P3, and retinoic acid‐related orphan receptor γt in patients with rheumatoid arthritis and reduce the disease activity score.^21^

Interestingly, recent animal studies have shown that ginger may have positive effects on MS activity. Jafarzadeh et al. (from 2014 to 2017) injected ginger extract at the doses of 200 and 300 mg/kg body weight intraperitoneally into mice induced with experimental autoimmune encephalomyelitis (MS animal model) for 28 days.^22^, ^23^, ^24^, ^25^ Findings from these studies have indicated that ginger supplementation can increase interleukin‐27 and transforming growth factor beta.^22^, ^24^ In addition, it can decrease the clinical symptoms of demyelination, CNS histopathological grades, interferon‐gamma, interleukin‐12, interleukin‐17, interleukin‐23, and interleukin‐33.^22^, ^23^, ^24^ Moreover, ginger administration may reduce the expression of C‐C motif chemokine ligand (CCL) 20 and CCL22 and their receptors, C‐C motif chemokine receptor (CCR) 6 and CCR4, in the spinal cord.^25^ The positive effects of ginger in the MS animal model seem to be exerted through its anti‐inflammatory, antioxidant, neuroprotective, and immunomodulatory properties.^26^

Despite the promising effects of supplementation with ginger in the MS animal model, to the best of our knowledge, no randomized controlled trial (RCT) has been conducted on this topic. Therefore, we aim to determine the impact of ginger supplementation on neurofilament light chain, matrix metalloproteinase‐9, interleukin‐17, nitric oxide, complete and differential blood counts, disability, quality of life, gastrointestinal symptoms, and BMI in patients with MS. The findings of this study will be helpful for people with or at risk of MS, researchers, and clinicians.

## METHODS

2

### Study aims

2.1

The main goal of this study is to determine the effect of supplementation with ginger on neurofilament light chain, matrix metalloproteinase‐9, interleukin‐17, nitric oxide, complete and differential blood counts, disability status, quality of life, gastrointestinal symptoms, and BMI in patients with relapsing‐remitting MS. The primary outcomes are interleukin‐17, nitric oxide, and disability status. The secondary outcomes are neurofilament light chain, matrix metalloproteinase‐9, complete and differential blood counts, quality of life, gastrointestinal symptoms, and BMI.

### Study design and status

2.2

The present study is a parallel double‐blind RCT. It started on 30 Jan. 2022 and is in progress.

### Study registration

2.3

This trial protocol was registered at www.irct.ir (Iranian Registry of Clinical Trials) on October 06, 2021 under the registration number IRCT20180818040827N3. It was planned and reported based on the Standard Protocol Items: Recommendations for Interventional Trials (SPIRIT) statement.^27^ The schedule of enrollment, interventions, and assessments according to the SPIRIT flow diagram is presented in Figure 1. The populated SPIRIT 2013 checklist is also provided in Supporting Information: Additional File 1.

**Figure 1 hsr21004-fig-0001:**
[figure not shown]
The SPIRIT figure for the schedule of enrollment, interventions, and assessments. SPIRIT, Standard Protocol Items: Recommendations for Interventional Trials.

### Study population and setting

2.4

The reference population in this trial will be adult patients with relapsing‐remitting MS. The patients will be recruited from Fars MS Association and Imam Reza (A.S) Clinic located in Shiraz, Iran. The prevalence of MS in Iran has been estimated at about 30 cases per 100,000 people.^28^ It has been reported that approximately 70% of Iranian MS patients suffer from the relapsing‐remitting type.^29^

### Sample size and sampling method

2.5

Given the study design and the existence of two independent groups, the following formula will be used to determine the required sample size:

$$n=\frac{{\left(Z_{1-\frac{\alpha }{2}}+Z_{1-\beta }\right)}^{2}\left(s_{1}^{2}+s_{2}^{2}\right)}{{\left(\mu_{1}-\mu_{2}\right)}^{2}}\;$$

Considering interleukin‐17 as one of the primary outcomes of this study, the number of samples in each of the intervention and control groups was determined to be 13 people (in total 26). The calculations were performed by assuming the type I error equal to 0.05 and the test power equal to 90% and by taking into account *S*
_1_ = 4.07, *S*
_2_ = 9.19, and the effect size equal to 9.28 based on the previous report.^30^

Considering nitric oxide as one of the primary outcomes of this trial, the number of samples in each of the intervention and control groups was determined to be 22 people (in total 44). The calculations were conducted by assuming the type I error equal to 0.05 and the test power equal to 90% and by taking into account *S*
_1_ = 0.72, *S*
_2_ = 0.19, and the effect size equal to 0.5 based on the previous report.^31^

Considering disability status measured by EDSS^9^ as one of the primary outcomes of the present study, the number of samples in each of the intervention and control groups was determined to be 22 people (in total 44). The calculations were done by assuming the type I error equal to 0.05 and the test power equal to 90% and by taking into account *S*
_1_ = 0.29, *S*
_2_ = 1.06, and the effect size equal to 0.74 based on the previous report.^32^

Finally, according to the maximum number of the samples (22 people in each group and 44 in total) and considering a drop‐out rate of ∼20%, the required sample size was estimated to be 26 patients in each group and 52 in total. The participants will be selected using convenience sampling method.

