### Participant allocation

2.8

The patients will be assigned to the treatment and control groups using stratified permuted block randomization (block size = 4, allocation ratio = 1:1). The stratification will be done according to gender (female or male). The following valid website will be used for generation of random allocation sequence: https://www.sealedenvelope.com/simple-randomiser/v1/lists. Placebo and ginger tablets will be sealed in sequentially numbered identical bottles based on the allocation sequence. The sequence generation, allocation concealment, and assignment of the patients to the groups will be implemented by different trained persons. The participants, researchers, care providers, and outcome assessors will be blinded to the group assignment.

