### Statistical analysis

2.13

SPSS Statistics software version 26 will be used for statistical analysis of data. The Shapiro–Wilk test and skewness will be applied to investigate the normal distribution of quantitative variables. Mean ± standard deviation or median [interquartile range] will be used to report quantitative variables, and number (percentage) will be used to report qualitative variables. For each outcome, the estimated effect size and its 95% confidence interval will be presented. The paired *t*‐test or Wilcoxon signed‐rank test will be performed to compare within‐group differences in quantitative variables. The independent *t*‐test or Mann−Whitney *U* test will be conducted to compare between‐group differences in quantitative variables. The analysis of covariance will be applied to compare between‐group differences by adjusting confounders. The Pearson *χ*
^2^ test or Fisher's exact test will be performed to compare between‐group differences in qualitative variables. All tests will be two‐tailed with a significance level of 0.05. The Statistical Analyses and Methods in the Published Literature (SAMPL) guideline will be followed for reporting statistical results.^46^

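### Randomising 26 per group leaves about 21 after the planned 20% drop-out, below the stated 22; separately, 22 is too few for 90% power on nitric oxide and EDSS

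*Protocol article*

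**What the plan says.** Section 2.5 (Sample size and sampling method) prints the usual normal-approximation formula for comparing two independent means and applies it to each of the three primary outcomes. The results are 13 per group for interleukin-17, 22 for nitric oxide and 22 for EDSS.

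For nitric oxide: "The calculations were conducted by assuming the type I error equal to 0.05 and the test power equal to 90" per cent. For EDSS: "The calculations were done by assuming the type I error equal to 0.05 and the test power equal to 90" per cent. The analysis section (2.13) confirms the two-sided level: "All tests will be two‐tailed with a significance level of 0.05". Allocation is equal (section 2.8: "allocation ratio = 1:1").

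Section 2.5 then takes the largest requirement, 22 per group and 44 in total, allows for a drop-out rate of about 20%, and states that "the required sample size was estimated to be 26 patients in each group and 52 in total". It does not show how the allowance was calculated. The abstract repeats the total of fifty-two.

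**The concern.** A drop-out allowance exists so that the number left at the end is still the number required. Here the required number, the drop-out rate and the number to randomise are all printed, and they do not fit together: losing a fifth of 26 leaves fewer than 22.

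The 22 itself also does not follow from the formula and inputs printed in the same section. Both slips run in the same direction. The 90% power stated for two of the three primary outcomes is therefore not what the design delivers under its own assumptions. A reader of a null result on nitric oxide or EDSS would credit the trial with somewhat more power than it had.

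**Working it through.** **Inputs (all from section 2.5 unless noted)**

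- Two-sided type I error 0.05 (also section 2.13) and power 90%, so (1.960 + 1.282)² = 10.507 (from unrounded quantiles).
- Nitric oxide: SDs 0.72 and 0.19, difference 0.5.
- EDSS: SDs 0.29 and 1.06, difference 0.74.
- Interleukin-17: SDs 4.07 and 9.19, difference 9.28.
- Required 22 per group; drop-out about 20%; randomised 26 per group.

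**Step 1: the drop-out allowance**

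The plan's 26 is reproduced by multiplying and rounding down: 22 × 1.20 = 26.4, then 26. The usual inflation divides by the proportion retained:

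- To keep 22: 22/(1 − 0.20) = 27.5, so 28 per group, 56 in total.
- What 26 leaves: 26 × 0.80 = 20.8, about 21 per group (52 × 0.80 = 41.6, about 42 in total, against the stated 44).
- Largest loss that still leaves 22: 1 − 22/26 = 15.4%.

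**Step 2: the base number, a separate matter**

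The printed formula is n = (Z₁₋α/₂ + Z₁₋β)²(s₁² + s₂²)/(μ₁ − μ₂)².

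- Interleukin-17: 10.507 × (16.565 + 84.456)/86.118 = 12.33, so 13. This matches the protocol and confirms that the printed effect size is the raw mean difference.
- Nitric oxide: 10.507 × (0.5184 + 0.0361)/0.25 = 23.31, so 24 (protocol: 22).
- EDSS: 10.507 × (0.0841 + 1.1236)/0.5476 = 23.17, so 24 (protocol: 22).

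Other settings do not recover 22 for nitric oxide or EDSS: one-sided at 90% gives 19, two-sided at 80% gives 18, and one-sided at 80% gives 14.

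**Step 3: power at the numbers in question**

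Inverting the printed formula with m completers per group gives power = Φ(difference/√((s₁² + s₂²)/m) − 1.960). For nitric oxide with m = 21: 0.5/√(0.5545/21) = 3.077, less 1.960 = 1.117, and Φ = 86.8%.

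| Completers per group | Nitric oxide | EDSS | Interleukin-17 |
|---|---|---|---|
| 24, formula | 90.8% | 91.0% | 99.5% |
| 22, formula | 88.3% | 88.5% | 99.1% |
| 21, formula | 86.8% | 87.0% | 98.8% |
| 21, pooled t-test | 85.1% | 85.3% | 98.5% |
| 21, Welch t-test | 83.8% | 84.0% | 98.3% |

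**Step 4: separating the two slips (formula scale)**

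- Using 22 instead of 24: about 88.3–88.5% instead of the stated 90%, before any drop-out error.
- Ending with 21 instead of 22: a further 88.3 − 86.8 = 1.5 points for nitric oxide and 88.5 − 87.0 = 1.5 points for EDSS.

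**The case against.** The best defence is that the rate is only approximate and the method of inflation is not stated. Four patients added to 22 is 4/22 = 18%, so the authors may have meant that roughly 20% was added. This makes the slip understandable, but it does not repair the text. The section speaks of a drop-out rate, which applies to those randomised, and 15.4% is too far from 20% to be covered by the approximation. That 22 was multiplied by 1.2 and rounded down is a likely explanation, but still an inference.

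The defence is right about size. The drop-out step costs about one completer per group, interleukin-17 is hardly touched, and no endpoint or analysis changes.

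Three stronger readings are tempting, and the documents do not support them.

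- A reader might infer that the drop-out error by itself defeats the 90% power. It does not: with exactly 22 completers, power is already about 88%, because of the base number.
- A reader might combine both slips and conclude that the trial must enrol 24/0.80 = 30 per group. That follows only if 90% is to be kept for every primary outcome. The drop-out correction on its own terms is 28, and restating the power needs no enrolment at all.
- Section 2.6 lists among the exclusion criteria events that occur during the intervention (an MS attack, a change of MS medication, tablet intake under 90%), and a reader might infer that losses will exceed 20%. The article does not say whether such patients leave the analysis or are already counted in the 20%, so nothing can be built on this.

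**Conclusion.** The point holds as a minor correction. At the protocol's own drop-out rate, 26 randomised per group leaves about 21, not 22. Separately, the printed formula needs 24 rather than 22 for nitric oxide and EDSS. Together they put power for these two outcomes at about 87% by the protocol's formula, or about 84–85% by t-tests, against the stated 90%. Interleukin-17 remains at about 98–99%.

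This rests on the printed SDs and differences, a 20% loss spread evenly over the groups, and analysis of completers only. If loss stays at or below 15.4%, 22 per group are retained, but power is then still about 88%. The design is not invalidated; what is wrong is a stated sample size justification and a stated power.

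**What to change.** Replace the last step of section 2.5 with a statement that 52 randomised with about 20% loss gives about 21 analysed per group. Give the resulting power as about 87% for nitric oxide and EDSS by the protocol's normal-approximation formula (about 85% by a pooled t-test, about 84% by Welch) and about 98–99% for interleukin-17. Correct the 22 to 24 where the formula is applied to nitric oxide and EDSS, and remove the claim that the planned size gives 90% power for them. Name the method beside each power figure so that it can be reproduced from the printed formula.

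Do not merely reword the allowance to say that 26 covers a 15% loss from 22. That would make the drop-out arithmetic consistent but leave the 90% claim wrong.

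The cost is a short text correction and a slightly lower stated power. The trial is already running, and no additional enrolment is required.

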### Inclusion and exclusion criteria

2.6

The inclusion criteria will include patients with relapsing‐remitting MS according to the 2017 McDonald diagnostic criteria,^33^ age between 18 and 50 years, non‐menopausal women or men, EDSS less than or equal to 4.5,^9^ no MS attack or corticosteroid therapy for at least the last 3 months, no change in the type or dose of MS medications for at least the last 6 months, and the ability and willingness to participate in the study.

The exclusion criteria will include MS patients with other serious diseases (e.g., autoimmune disorders or cancers), pregnancy, MS attack or corticosteroid therapy during the intervention, changes in the type or dose of MS medications during the intervention, supplementation with antioxidants or nutrients (except vitamin D), allergic reactions to ginger or placebo tablets, and consumption of less than 90% of ginger or placebo tablets.

### Run‐in period

2.7

The participants will be undergone a 3‐week run‐in period before random allocation to the treatment or control group for 12 weeks. During the run‐in period, the patients will be asked to avoid consuming ginger and its products and to maintain their usual diet and physical activity.

### Participant allocation

2.8

The patients will be assigned to the treatment and control groups using stratified permuted block randomization (block size = 4, allocation ratio = 1:1). The stratification will be done according to gender (female or male). The following valid website will be used for generation of random allocation sequence: https://www.sealedenvelope.com/simple-randomiser/v1/lists. Placebo and ginger tablets will be sealed in sequentially numbered identical bottles based on the allocation sequence. The sequence generation, allocation concealment, and assignment of the patients to the groups will be implemented by different trained persons. The participants, researchers, care providers, and outcome assessors will be blinded to the group assignment.

### Intervention

2.9

The intervention and control groups will take 500 mg ginger and placebo (corn) tablets three times a day for 12 weeks, respectively. The subjects will be asked to take each of the three tablets along with one of the main meals including breakfast, lunch, and dinner. The dose and duration of ginger supplementation were chosen based on a previous study conducted in patients with active rheumatoid arthritis, which is an autoimmune inflammatory disorder similar to MS.^31^ Appearance characteristics such as packaging, size, shape, and color of placebo tablets will exactly be the same as ginger tablets. Moreover, a very small amount of ginger powder will be poured into each of the boxes containing placebo tablets to make them smell alike, as previously used by Ebrahimzadeh Attari et al.^17^, ^34^ and Mahluji et al.^35^ Both ginger and placebo tablets will be provided by Dineh Iran Industries Complex, Tehran, Iran. Each 500 mg ginger tablet is standardized to contain 25 mg gingerols.

